### Study design

3.1

This study is a multicenter, prospective cohort study. The study has started in March 2016 and is currently ongoing. Two hundred and twenty TNBC patients aged between 18 to 75 years with II-III stage after surgery are enrolled from 9 hospitals. All participants need to complete the standard chemotherapy and (or) radiotherapy specified by the National Comprehensive Cancer Network (NCCN) guidelines according to their disease states. At the time of the participants entered the study, the duration of the last chemotherapy and (or) radiotherapy was not more than half a year. The whole study consists of 2 stages, stage I comprises a cross-sectional study-baseline and stage II is a cohort follow-up study across a 3-year period. Participants will be followed up every 3 to 6 months till recurrence or metastasis for 3 years. The feasibility and preciseness of the whole process were supervised by 1 to 2 supervisors.

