### Sample size calculation

3.5

The primary objective of the research is 3-year DFS rate and we use it as the basis for the calculation of sample size. Referring to the relevant large-scale cohort study,^[18]^ the 3-year DFS rate of TNBC patients after surgery is about 77%, we assume it to be increased to 86%^[19]^ with the treatment of CHM. The sample size calculation formula for cohort study is n = 2p(1-p)(uα + uβ)/(p1-p2),^[2]^ p = (p1 + p2)/2, α assign to 0.05 and β assign to 0.2, the power is 80%, we need 92 participants of each cohort. The drop-out rate is considered as 20%, then the sample size of each cohort is 110 and the total sample size is 220.

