### Observation time

3.7

Primary endpoint: Local recurrence or distant metastasis.

Study endpoint: Local recurrence or distant metastasis, death, or the end of the study.

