### Statistical analysis

3.8

All statistical analysis will be performed using Statistical Packages of Social Sciences software (SPSS) 19.0. Statistical significance will be defined as the *P* < 0.05. Based on the data distribution, the measurement data will be analyzed by ANOVA or *U* Mann-Whitney test, counting data using *χ*^*2*^test or *U* Mann-Whitney test. The survival data will be analyzed by Kaplan-Meier method in 1, 2, 3-year DFS rate and the recurrence and metastasis rate, then draw the survival curve. The comparison of survival curves between the two cohorts is based on Log-rank method. Repeated ANOVA will be used to evaluate the repeated measures such as the QoL, physical condition, and symptoms related to breast cancer. Evaluation of therapeutic efficiency will be analyzed by the data of full analysis set (FAS) and per protocol set (PPS), safety evaluation will use the data of safety analysis set (SS) for statistical analysis.

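### Repeated-measures ANOVA for QoL, ECOG and symptom scores does not fit follow-up that ends at recurrence; in its standard form it would compare mainly recurrence-free patients with complete follow-up

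*Protocol article*

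**What the plan says.** Section 3.8 (Statistical analysis) of the protocol article assigns the longitudinal scores to a single method: "Repeated ANOVA will be used to evaluate the repeated measures such as the QoL, physical condition, and symptoms related to breast cancer". These scores carry both secondary objectives in section 2.2: quality of life (FACT and ECOG), and fatigue, sleep, depression and anxiety. Section 3.4.2 describes ECOG as a score from 0 to 5.

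Follow-up is set in section 3.1: "Participants will be followed up every 3 to 6 months till recurrence or metastasis for 3 years". Section 3.7 adds death and study closure: "Study endpoint: Local recurrence or distant metastasis, death, or the end of the study".

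Section 3.5 gives the expected losses. Without CHM, "the 3-year DFS rate of TNBC patients after surgery is about 77" per cent; with CHM, "we assume it to be increased to 86" per cent. For loss to follow-up, "The drop-out rate is considered as 20" per cent, with 110 patients planned in each cohort.

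Section 3.8 names a full analysis set and a per-protocol set for efficacy. The article does not say how incomplete score series, or scores after recurrence, would be handled.

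**The concern.** Standard repeated-measures ANOVA works on a rectangular table: every patient has a score at every common time point, and a patient with a gap is left out entirely. This design makes gaps certain. A patient whose disease returns has no later scores because the plan stops following her, and others drop out.

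Loss through recurrence is tied to prognosis, and probably to the scores themselves, so the patients left are not a random subset. The cohorts are defined by whether patients take CHM, not by randomisation. If CHM works as assumed, recurrence removes more patients from one cohort than from the other. A difference in mean scores between the remaining groups could then reflect who is left as well as any association with CHM.

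Both secondary objectives rest on this analysis. Dropping incomplete patients would also discard scores already collected, in a study whose Discussion concedes that its sample looks small.

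A lesser weakness is that ECOG, a short ordinal scale, goes through an analysis meant for continuous measurements.

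**Working it through.** The article states no figure for the repeated-measures analysis, so there is none to reproduce. The question is what share of each cohort could have complete scores to year 3 on the plan's own rates.

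**Inputs (section 3.5).** 3-year disease-free survival S = 0.77 without CHM and 0.86 with CHM; drop-out d = 0.20; n = 110 per cohort.

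**Step 1: recurrence or death alone.** The share still observed is S.
- No CHM: 0.77 × 110 = 84.7
- CHM: 0.86 × 110 = 94.6
- Total: 179.3 of 220 = 81.5%

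**Step 2: add drop-out.** The article does not say how drop-out relates to recurrence, so three cases are shown.

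| Assumption | Formula | No CHM | CHM | Both cohorts |
|---|---|---|---|---|
| No overlap | S − d | 0.77 − 0.20 = 57% (62.7) | 0.86 − 0.20 = 66% (72.6) | 135.3/220 = 61.5% |
| Independent | S × (1 − d) | 0.77 × 0.80 = 61.6% (67.8) | 0.86 × 0.80 = 68.8% (75.7) | 143.4/220 = 65.2% |
| Full overlap | min(S, 1 − d) | min(0.77, 0.80) = 77% (84.7) | min(0.86, 0.80) = 80% (88.0) | 172.7/220 = 78.5% |

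Even the most favourable case loses 100 − 78.5 = 21.5% of patients; independence loses 34.8%. The gap between cohorts is 3 points under full overlap, 7.2 under independence and 9 under no overlap.

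**Step 3: sensitivity to the drop-out input.** The planned 110 corresponds to 92 × 1.2 = 110.4, so the allowance actually made is 18/110 = 16.4%, not 20%. Under independence that gives 0.77 × 92/110 = 64.4% and 0.86 × 92/110 = 71.9%. The conclusion is unchanged. Nothing here depends on how the 92 was derived.

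**Step 4: visit timing.** Over 36 months, 6-monthly visits give 36/6 = 6 and 3-monthly visits give 36/3 = 12. If patients follow different spacings, they share no common grid. Whether they do depends on the schedule in Table 2, which is not visible.

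**The case against.** The strongest reply is that the article never says incomplete patients are deleted. It names a method and a full analysis set, and handling of missing data is commonly left to a full protocol or SAP. That stands in part: deletion is a property of the standard procedure, not a rule written in the plan, and a fuller document could add imputation. But naming a full analysis set does not keep an incomplete patient in a repeated-measures ANOVA, and the method itself is fixed here.

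Second, Table 2 may set common questionnaire visits. That would ease or remove the timing problem. It would not remove truncation at recurrence or loss through drop-out.

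Third, the Discussion acknowledges possible baseline imbalance and promises analysis by stage, age and other factors, and a cohort-by-time term compares changes from baseline. So confounding is partly addressed and adds little weight here. Neither measure restores patients who are dropped or cut off.

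Fourth, the Discussion promises observation beyond three years. It does not say that scores are collected after recurrence.

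Stronger readings are tempting but unsupported. A reader might take 62% and 69% as maxima; they hold only under independence, and more overlap raises them. A reader might multiply in missed single visits and conclude that fewer than half, or even fewer than a fifth, would be complete. Missed visits could only lower the share, but the article gives no rate for them, so such figures would describe the assumption and not the plan.

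**Conclusion.** The concern holds as a mismatch between a method the plan fixes and the follow-up it describes. Analysed in the standard way, the secondary comparisons would rest on recurrence-free patients with complete follow-up: about 62% without CHM and 69% with CHM under independence, with ranges of 57–77% and 66–80% across the possible overlaps.

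This rests on three assumptions: the standard complete-visit form of the analysis, the plan's own event and drop-out rates, and no score collection after recurrence. The inequality between cohorts follows from the plan's hypothesis that CHM improves disease-free survival. If the true rates were equal, the selection by prognosis would remain, but recurrence need not remove unequal shares.

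A reader might infer a bias of known direction or size; the documents do not allow that. A reader might also infer that the primary result is compromised. It is not: disease-free survival is analysed by Kaplan-Meier and log-rank, and only the secondary outcomes are affected. The change should be made, but the trial's main question does not depend on it.

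**What to change.** In section 3.8, replace repeated ANOVA with:

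- **QoL and symptom scores:** a linear mixed model using every available score, with actual time since enrolment, cohort, cohort × time, baseline score, and the factors the Discussion already names (stage and age). The covariates must be listed explicitly, because the planned primary analysis is unadjusted and offers no set to carry over.
- **ECOG:** an ordinal mixed or GEE model, or the same with ECOG dichotomised (0 versus 1 or more).
- **Target:** a statement that the quantity of interest is the score while the patient is recurrence-free.
- **Sensitivity analysis:** one for truncation at recurrence or death. This is needed because the mixed model assumes data missing at random and implicitly extrapolates scores past recurrence, so it does not by itself deliver the stated target. One option is a GEE with independence working correlation on the scores observed before recurrence, weighted for drop-out.

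The cost is a change of wording and some extra analysis in standard software, with no new data or visits. The price is reliance on the missing-at-random assumption, which is weaker than what a complete-visit ANOVA needs but still untestable; hence the sensitivity analysis.

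### Repeated ANOVA for quality of life and symptoms would drop about one third of patients, those who recur or drop out, from a 3-year analysis; a mixed model on all collected scores would keep them

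*Protocol article*

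**What the plan says.** - **Method (3.8, Statistical analysis).** "Repeated ANOVA will be used to evaluate the repeated measures such as the QoL, physical condition, and symptoms related to breast cancer". The section names no method that keeps incomplete series. It fixes the software: "All statistical analysis will be performed using Statistical Packages of Social Sciences software (SPSS) 19.0". It also says that efficacy will be assessed in the full analysis set (FAS) and the per-protocol set.
- **Follow-up (3.1, Study design).** "Participants will be followed up every 3 to 6 months till recurrence or metastasis for 3 years".
- **Exit (3.7, Observation time).** "Study endpoint: Local recurrence or distant metastasis, death, or the end of the study".
- **Planning rates (3.5, Sample size calculation).** "the 3-year DFS rate of TNBC patients after surgery is about 77%, we assume it to be increased to 86"% with CHM. For losses: "The drop-out rate is considered as 20%, then the sample size of each cohort is 110 and the total sample size is 220".
- **Outcomes concerned (2.2 and 3.4.2).** FACT, ECOG status, fatigue, sleep, depression and anxiety, each in relation to CHM use.

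**The concern.** Classical repeated-measures ANOVA, as in the SPSS general linear model procedure, works on a rectangle: one column per visit and one complete row per patient. A patient with one empty cell is removed together with all scores already given.

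The design produces incomplete rows by rule. A patient who recurs leaves follow-up, and a patient who drops out leaves it too. The patients who stay in the analysis are therefore selected by what happens after baseline, partly by the primary outcome itself. The plan expects that outcome to differ between two cohorts that were not randomised.

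At stake is the meaning of the longitudinal secondary comparisons. A CHM difference in quality of life or symptoms would be estimated in recurrence-free completers only, and could be created or hidden by the selection. Valid scores from the other patients would be thrown away.

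**Working it through.** **Plan's own figure.** The article gives no number of patients for the repeated-measures analysis, so there is none to reproduce. The starting point is the planned 110 per cohort, which matches 92 × 1.2 = 110.4. (The 92 does not follow from the formula in 3.5 with its squares, which gives about 292 per cohort for a two-sided test. That is a separate matter and does not change the proportions below.)

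**Inputs from 3.5.** 110 patients per cohort; 3-year disease-free survival 0.77 without CHM and 0.86 with CHM; drop-out 0.20.

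**Failures by year 3.** 1 − 0.77 = 23% and 1 − 0.86 = 14%.

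**Complete to year 3 if recurrence and drop-out are independent:** n × DFS × (1 − drop-out).
- Without CHM: 110 × 0.77 × 0.80 = 67.8
- With CHM: 110 × 0.86 × 0.80 = 75.7
- Total: 143.4 of 220 = 65%. Excluded: 220 − 143.4 = 76.6, about 77 patients.
- Exclusion by cohort: 1 − 0.77 × 0.80 = 38% and 1 − 0.86 × 0.80 = 31%.

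**Range over the overlap of the two losses.**

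| Overlap | Without CHM | With CHM | Total of 220 |
|---|---|---|---|
| None: n × (DFS − 0.20) | 62.7 | 72.6 | 135.3 (62%) |
| Independent | 67.8 | 75.7 | 143.4 (65%) |
| Maximal: n × min(DFS, 0.80) | 84.7 | 88.0 | 172.7 (79%) |

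**Missed visits.** The article gives no attendance rate, so these figures rest on an assumption. Multiply 143.4 by attendance to the power of the number of visits. Six visits correspond to 6-monthly and twelve to 3-monthly follow-up over 3 years.
- 95% attendance: about 105 (6 visits) or 78 (12 visits)
- 90% attendance: about 76 or 41

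**Precision, as illustration only.** Simulations assumed 6 visits, score SD about 20 and within-patient correlation 0.5. None of these values is in the article. Compared with a likelihood model on all scores, the standard error of the complete-case cohort contrast was 16% to 20% larger with no missed visits, and 38% to 39% larger with 5% missed visits.

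**The case against.** **Missing-data handling belongs in the analysis plan, and the FAS is named.** An article may leave imputation rules to a document not shown. But 3.8 does more than stay silent: it names a method which in its ordinary form deletes incomplete series. Naming the FAS does not repair this, because listwise deletion would not analyse the FAS for these outcomes. The point stands as a comment on a stated method.

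**Few patients would be left.** A reader might infer this, but the plan's own rates do not support it: about 65% remain, with a range of 62% to 79%. Much lower counts need an assumed attendance rate.

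**The visit schedule cannot supply common time points.** It is tempting to read the 3-to-6-month interval as 6 to 12 visits per patient at unaligned dates. The data collection schedule is in Table 2, whose content is not visible in the text reviewed, and it may fix common months for the questionnaires. The interval could also be one shared schedule with changing spacing. The spacing argument is therefore conditional. Nor does the article suggest that the cohorts are seen at different intervals.

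**All secondary results are affected.** This is too broad. Stage I is a cross-sectional baseline study that uses everyone enrolled, and 3.8 provides ANOVA or Mann-Whitney tests for other measurement data. Only the longitudinal comparisons are touched.

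**A false CHM benefit will result.** A simulation can produce one, for example when drop-out follows scores in opposite directions in the two cohorts. That is a constructed case. The documents support possible bias, not its direction or size.

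**A mixed model does not solve truncation.** This stands. No scores are planned after recurrence, so a model that assumes data missing at random extrapolates recurrence-free trajectories past recurrence or death. The fix must address this.

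**Conclusion.** The point holds for the longitudinal secondary outcomes. A classical repeated ANOVA over 3 years would exclude about one third of patients with all their earlier scores: about 77 of 220, or between 47 and 85 depending on overlap. Expected exclusion is about 38% without CHM and 31% with CHM under independence. The exclusion depends on the primary outcome and is at odds with the FAS statement, taking the efficacy analyses to include these scores.

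The size rests on four assumptions: the planning rates of 3.5 apply from study entry, drop-out is 20% in both cohorts, recurrence and drop-out are independent (otherwise the range above), and the analysis runs to year 3. If Table 2 does not fix common questionnaire time points, the 3-to-6-month spacing adds misaligned or missing visits, by an amount the article does not allow one to compute. The primary outcome analysis is not affected. The change should be made, since it is cheap and replaces a method poorly suited to the design.

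**What to change.** In 3.8, replace repeated ANOVA by a linear mixed model fitted to every score collected in the FAS.
- Use actual months since baseline as the time axis, or fixed analysis windows.
- Include cohort, time and cohort-by-time terms and a within-patient covariance.
- State the cohort contrast at a fixed month and report the number of scores behind it in each cohort.
- Interpret the result as quality of life and symptoms while recurrence-free, or add a sensitivity analysis, for example a joint model, for truncation by recurrence or death.
- Keep complete-case repeated ANOVA only as a sensitivity analysis.

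The cost is a few lines of text and slightly more analysis work, with no extra patients, visits or data. The mixed model can be fitted in the SPSS package already named; a joint model may need other software. The mixed model assumes that missingness is explained by the observed data. That is weaker than what listwise deletion needs, but still an assumption that recurrence may violate, hence the interpretation or sensitivity analysis above.

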## Discussion

4

CHM has been used for thousands of years in China. In recent years, it has been gradually accepted by Western countries.^[20]^ Thus far, literatures^[21,22]^ reported that CHM is widely used to reduce the side effects of chemotherapy and increase survival of patients, antitumor immune response and the general state of the patients. Also, research^[23]^ reported that CHM combined with chemotherapy can improve survival rate and the quality of life. To evaluate the relationship between CHM and tumor recurrence and metastasis, we choose a simple disease TNBC as the research type. So far it has no other therapeutic regimen besides chemotherapy and radiotherapy after surgery and we can eliminate interference from other treatment factors.

There are several strengths in our study. First, this is the first multicenter prospective observational cohort study on CHM in TNBC patients. There are 9 hospitals participating in this study. It can provide the evidence both relatively objective and consistent with the clinical practice of CHM intervention for TNBC. Second, we choose the observational study design as it is more humanistic than randomized controlled trial (RCT). Although RCT is recognized as the highest level of evidence in the field of evidence based medicine (EBM), it faces a series of ethical challenges for patients with cancer, especially for the research related to survival time. However, the observational cohort study greatly values individual willingness for the choices of treatment and maximize the applicability of CHM in clinical practice.^[24]^ Third, doctors write out a prescription based on the patient's TCM syndrome differentiation^[25]^ instead of roughly dividing into a few types of syndrome. This improves not only the accuracy of syndrome differentiation, but also the pertinence of CHM. Lastly, the study will produce a scroll queue of TNBC that is not only used for this study, but the relevant information from the rolling queue will continue to be followed up and recorded to provide effective and detailed information for the subsequent researches.

Some limitations of this study are as follows. In the field EBM, the cohort study is an observational study and the evidence level is lower than RCT.^[26]^ But after weighing the research program and the patients’ interests, we choose to maximize the latter one to use a cohort study. In addition, there may be an imbalance baseline condition between the two cohorts. To resolve the problem, we will analyze the data at different levels according to different stages of disease, age, and other possible related factors. Since it is a cohort study, queue migration is inevitable. Strengthening the management of follow-up of participants is one of the effective ways to avoid the problem. Patients will be followed up every 3 to 6 months, their medication and physical conditions will be recorded in detail in the CRF. Finally, there are only 220 TNBC patients will be recruit and the sample size looks small for a prospective cohort study. Yet it is limited by research period and funding. Nevertheless, the observation for the TNBC participants take part in this study won’t be stopped three years later. We will continue to follow up these participants to get a long-term information and then to analyze and evaluate the effect of TCM on TNBC more accurately.
